## Abstract

**Background::**

The patient's pattern identification has been used for personalized medicine in traditional Korean medicine (TKM) and aims for patient-specific therapy by Korean medical doctors. The pattern identification in this trial will be diagnosed from body constitution questionnaire (BCQ) with a more objective diagnosis of it but this method still needs a more concrete scientific basis. Glycoproteins are well-known to be associated with diseases (especially cancers) so glycoproteomics can be applied to differentiate pattern identification types of lung cancer patients. Thus, for the first time proteomics approach will be applied to the pattern identification by comparing BCQ assessment in order to establish a scientific basis with clinical proteomics for precision medicine.

**Methods::**

This observational trial will at first diagnose the pattern identification types of lung cancer patients with BCQ assessment and then elucidate their relationships with proteomics. Blood samples will be collected before surgery along with clinical information of participants. The patients’ pattern identification in TKM will be diagnosed from BCQ assessment. Then, lung cancer patients will be divided and pooled into 3 lung cancer entire (LCE) groups according to their pattern identification types (Xu, Stasis, or Gentleness). Three lung cancer representative (LCR) groups will be selected and pooled from each LCE group by selecting those with the same control factors. The 3 LCE groups and the 3 LCR groups from lung cancer patients will be independently analyzed through the glycoproteomics approach based on the patients’ pattern identification. Glycoproteins from the 6 groups will be identified through proteomics approach and then categorized for analysis.

**Discussion::**

This study intends to diagnose pattern identification of patients in TKM with BCQ assessment and proteomics approach. The identification of the glycoproteins in each group will lead to the scientific foundation of personalized medicine in TKM according to patients’ pattern identification for lung cancer therapy. We intend to

(1) diagnose the pattern identification types of lung cancer patients with BCQ under the framework of TKM;

(2) evaluate BCQ assessment with glycoproteomics approach for precision medicine.

**Trial registration::**

ClinicalTrials.gov NCT03384680. Registered 27 December 2017. Retrospectively registered.

## Introduction

1

Chemotherapy as a conventional treatment aims for reduction, suppression, and removal of cancer, but cancer patients commonly suffer from severe side effects from it. Furthermore, in cancer patients, tumor-induced symptoms and chemotherapy-induced symptoms are often manifested in combination.^[1]^ Therefore, there has been an increasing demand for complementary and alternative medicines from both Korean medical doctors and patients to relieve cancer pain and side effects during the treatment. This will eventually improve the quality of life of cancer patients.^[2]^ The treatments based on traditional Korean medicine (TKM), a branch of complementary and alternative medicines, have been successfully applied to cancer patients to control the side effects of antineoplastic medicine in combined Oriental and Western medicine (COWM).^[3–4]^ Compared to Western medicine, TKM is fundamentally different in the treatment process for cancer patients; there is an important step of “pattern identification” for patient-specific diagnosis and medication. Pattern identification is a practice in TKM where the treatment is determined after the body constitution of the patients and their symptoms are holistically examined.^[5]^ These treatments are generally determined by the patients’ pattern identification as well as the diagnosed disease and are thus personalized medicine. Precision medicine, also known as personalized medicine, is an emerging treatment strategy targeted to the needs of individual patients on the basis of genetic, biomarker, phenotypic, or psychosocial characteristics that distinguish a given patient from other patients with similar clinical presentations.^[6–7]^ Therefore, Asia including Korea has already been using precision medicine according to patients’ pattern identification type traditionally, and TKM determined by pattern identification is a precision medicine by itself.

Pattern identification of each patient has not been widely applied to clinical trials in which objective criteria are important.^[8]^ But since clinical trials using pattern identification are gradually increasing as the importance of precision medicine is being recognized^[9]^, there has been studies using pattern identification in clinical trials for cancer patients.^[10]^ Also, traditionally diagnoses of pattern identification relied on patients’ subjective descriptions and doctors’ subjective judgments^[11–13]^, many studies on questionnaires such as body constitution questionnaire (BCQ) have been developed.^[14–17]^ This BCQ has been utilized to the clinical studies including breast cancer^[18]^, liver cancer^[19]^, diabetes^[20–22]^, schizophrenia^[23]^, and menopausal symptoms^[24]^, as well as healthy control groups^[25]^. BCQ enables us to assess patients’ pattern identification types according to their body constitutions using 19 to 23 simple-to-answer (survey) questions. This pattern identification tool can be more objective compared to the examination by individual TKM doctors.^[26–28]^ However, BCQ still requires a proven scientific basis for determining pattern identification of patients as well as wide acceptance from the TKM community. This study intends to find a scientific standard on the pattern identification of lung cancer patients in the framework of TKM.

Lung cancer was reported to be ranked first in both the number of new cases and the number of deaths for both genders among 36 types of cancers (excluding non-melanoma skin cancer) in 2018 which was estimated by The International Agency for Research on Cancer (IARC) to inform about cancer control and cancer research from 186 countries.^[29]^ For males, in particular, lung cancer also leads all other cancers in both the number of new cases and the number of deaths. It is notable that for both genders, the number of deaths from lung cancer is more than twice that of colorectum cancer, the second-tier in the number of deaths.^[30]^ In Korea, lung cancer is also the leading cause of death for both genders among the 24 types of cancers according to recent cancer statistics reports jointly published by Ministry for Health and Welfare and National Cancer Center of South Korea in 2018.^[31]^ These cancer statistics illustrate that lung cancer causes the largest number of deaths worldwide and indicate the importance of lung cancer therapy for cancer patients worldwide.

Cancer-associated glycoproteins have been reported to be shed into blood and lymph.^[32–33]^ Since glycans in glycoproteins are significantly altered in cancer^[34]^, they may serve as a tool for judging chemotherapy efficacy. Recent studies have reported changes in α-1-antitrypsin (A1AT) glycosylation in lung cancer serum, tissues, and cell lines.^[35–37]^ According to this study, a lectin microarray was used to detect glycosylation changes in serum A1AT from patients with lung adenocarcinoma (ADC), squamous cell lung cancer, small-cell lung cancer (SCLC), and benign pulmonary diseases. Differentially expressed glycosylated patterns of A1AT were identified by lectin arrays and were confirmed by lectin-based enzyme-linked immunosorbent assay (ELISA). This observational study is supported by these studies and suggests that the glycoproteomics approach may identify glycosylation differences among the 3 different pattern identification types in lung cancer plasma. Lung cancer patients will be pooled based on their pattern identification types diagnosed with BCQ assessment and then the glycoproteomics approach will be applied to each pooled pattern identification plasma.

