#### Control factors

2.7.2

Glycoproteins in blood can vary qualitatively and quantitatively by numerous variables such as sex, age, and medical history. The glycoproteins must be qualitatively and quantitatively analyzed based on the pattern identification of the lung cancer patients. We hypothesize that each pattern identification of TKM as well as other variables such as sex, age, medical history, and etc. affects glycosylations on plasma proteins. Therefore, all the other variables other than pattern identification must be strictly controlled.

Since it is impossible to control all of the 19 variables of clinical information, we need to select as many variables as possible that are within our control. For example, smoking can be selected as the control factor that is closely related to lung cancer while sex ratio and average age can be considered as basic control factors for qualitative and quantitative analysis of glycoproteins. Both TNM stage and cancer subtype can be selected as control factors. Disease histories can be selected as control factors that can affect glycosylation in cancer plasma. Patients with no prior history of cancers other than lung cancer will be selected because other cancers may affect the aberration in the glycan moieties of glycoproteins in the plasma. Cancer histories from direct family can be considered as a genetic factor.

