### Glycoprotein capture

2.10

Glycoprotein capturing lectin column will be self-packed and connected to high performance liquid chromatography (HPLC) system for lectin affinity chromatography (LAC). Pooled human plasma from lung cancer patients will be loaded directly onto the column with mobile phase. The detailed affinity chromatographic method will follow the method section of the reference paper.^[43]^

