### Trypsin digestion and deglycosylation with PNGase F

2.11

The selected proteins will be digested with sequencing grade trypsin for protein digestion and then with PNGase F for deglycosylation of glycoproteins. The detailed proteomics method will follow the method section of the reference paper.^[44]^ The PNGase F-treated peptide mixtures will be stored at −80°C until analyses.

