### nLC-MS/MS methods for protein identification

2.12

The PNGase F-treated peptide mixtures from the 6 groups (LCEX, LCES, LCEG, LCRX, LCRS, and LCRG) will be analyzed with a nano liquid chromatography-tandem mass spectrometry (nLC-MS/MS). Each sample will be run more than twice under the identical conditions. The operational instruments and detailed methods will be in the method section of the reference paper.^[45]^

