### Statistical analysis with database searches

2.13

After at least 2 MS/MS data are obtained from each sample, protein identification will be performed with 2 complementary database search programs. Both Proteome Discoverer 1.4 (Thermo Fisher Scientific Inc., USA) and ProteinPilot 5.0 (SCIEX, USA) will be used to identify proteins from MS and MS/MS spectra. Each software program has its own unique analysis algorithm. Thus, it will be meaningful to compare the results from the 2 programs because it will reinforce the confidence of the identified proteins. At least 4 data files with identified proteins will be produced from each sample. Each data file will be individually sorted and filtered under the following conditions:

(1)dynamic modification option: deamidated (N-glycosylation)(2)peptide confidence levels: the peptide is significant only if (a) confidence levels are over 95%, or (b) confidence levels are below 95% in 2 runs but show significant MS/MS spectra.(3)proteins inclusion and exclusion: for Proteome Discoverer software, only the proteins with protein scores of 6.0 or higher will be included; for ProteinPilot software, only the proteins with the unused values of 2.0 or higher will be included. The rest of the identified proteins will be excluded from the results.

Starting with the significant data from the 2 software programs, only the peptides/proteins with N-glycosylation sites will be selected and used for the parent protein identification. These glycoproteins will be sorted and compared within each group (Xu, Stasis, and Gentleness). Then these proteins will be sorted into those that are identified in all LCE groups, all LCR groups, and only certain group(s). The resulting 6 N-glycoprotein lists will be used for the following 5 comparative analyses:

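### The hypothesis concerns glycosylation, but pattern types are compared only by lists of parent proteins after the glycans are removed, so a glycosylation change can show only indirectly

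*Protocol article*

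**What the plan says.** **Expectation and hypothesis.** The Introduction of the protocol article builds its rationale on altered glycosylation of a single serum protein, alpha-1-antitrypsin (A1AT), in lung cancer. Of that precedent it reports: "Differentially expressed glycosylated patterns of A1AT were identified by lectin arrays". It then suggests that "the glycoproteomics approach may identify glycosylation differences among the 3 different pattern identification types in lung cancer plasma". Section 2.7.2 (Control factors) goes further and hypothesizes that pattern type, along with other variables such as sex and age, "affects glycosylations on plasma proteins". The same section adds: "The glycoproteins must be qualitatively and quantitatively analyzed based on the pattern identification of the lung cancer patients".

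**Laboratory path.** Section 2.10 uses lectin affinity for capture: "Glycoprotein capturing lectin column will be self-packed". In section 2.11 the captured proteins are digested with trypsin and "then with PNGase F for deglycosylation of glycoproteins". Under section 2.12, "The PNGase F-treated peptide mixtures from the 6 groups" are what the mass spectrometer measures.

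**Analysis path.** Section 2.13 searches with deamidation as the mark of N-glycosylation and applies confidence and score criteria. Then "only the peptides/proteins with N-glycosylation sites will be selected and used for the parent protein identification". This gives six N-glycoprotein lists, one per pool, which feed all five planned comparisons. Comparison (3) sets the entire groups against the representative groups. Comparisons (4) and (5) sort proteins into unique and intersection sets across Xu, Stasis and Gentleness.

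**The concern.** The rationale and the hypothesis are about how a given protein is glycosylated. The comparisons are about which proteins are listed. These are different quantities, and the motivating example falls in the gap between them: the A1AT precedent is a changed glycosylation pattern on one protein, read directly by lectin arrays. Here the lectin serves only to capture material, and no lectin readout is planned.

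Two errors of interpretation are at stake. A protein in the intersection could be taken to show no glycosylation difference between types, when the readout was not able to show one. A protein unique to one type could be taken as evidence of a glycosylation difference, when it shows only that the protein met the identification criteria in one pool and not in the others. The second matters because the Discussion (section 3) intends to treat the identified proteins as indicators of pattern type.

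**Working it through.** The plan gives no figure to reproduce, and no sample-size or error-rate formula applies. The check is to follow different kinds of change through sections 2.10 to 2.13 and see where each ends up.

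Inputs from the protocol article:
- Capture depends on the glycan (2.10); the lectin and elution details are left to a cited paper.
- Glycans are removed before measurement (2.11, 2.12). What remains of glycosylation in the data is the deamidation mark at the N-site.
- A peptide counts at over 95% confidence, or below that in two runs with significant spectra. A protein counts at a score of at least 6.0 (Proteome Discoverer) or an unused value of at least 2.0 (ProteinPilot). Only peptides or proteins with N-glycosylation sites are kept (2.13).
- Each entire-group pool holds at least 10 patients (2.8.1).

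| Change between pattern types | Parent-protein list (as planned) | N-glycosite list |
|---|---|---|
| Different glycan structure; protein still captured and same site still occupied in all pools | Intersection | Same in all pools; still not seen |
| One of two detectable sites lost in one pool; the other still identified | Intersection | Differs |
| Partial fall in lectin binding; protein still meets the criteria | Intersection | Same, unless a weaker site peptide drops out |
| Fall in lectin binding, or loss of the detectable site, that takes the protein below the criteria in a pool | Absent from that pool's list | Differs |
| Lower protein abundance, glycosylation unchanged, protein falls below the criteria in a pool | Absent from that pool's list | Differs |

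Three results follow.

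1. The first row is the A1AT type of change. If A1AT is captured from all three pools with different glycans, PNGase F removes them, the same deamidated peptide is identified, the same parent protein is listed, and it is placed in the intersection.
2. The fourth row shows that the readout retains some sensitivity to glycosylation. The route is indirect and depends on crossing an identification threshold in a whole pool.
3. The fourth and fifth rows look alike on the protein list, so a unique protein does not point to glycosylation in particular.

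The data for the last column already arise from the plan. Section 2.13 expects at least 4 result files per sample, so at least 4 × 6 = 24 files over the six pools, each filtered with deamidation as the N-glycosylation mark before parent proteins are named.

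**The case against.** The strongest reply is that outcome and analysis agree. Section 2.2.1 words its third primary outcome as identifying and categorizing proteins, section 2.13 delivers protein lists, and the Discussion speaks of identified plasma proteins. The Introduction's sentence is tentative background, and the hypothesis in 2.7.2 serves to justify controlling other variables. Section 2.8 calls the trial preliminary. This stands to a point: the mismatch lies between the hypothesis or rationale and the readout, not between the primary outcomes and the analysis. A reader might infer that the trial cannot answer its primary outcomes; the documents do not support that. But 2.7.2 does state a hypothesis about glycosylation, and none of the five comparisons reads it directly.

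A reader might also infer that the workflow is blind to glycosylation, or that a change registers only if lectin capture fails completely in a pool. Neither holds. Capture is glycan-selective, the deamidation mark indicates an occupied site, and the thresholds mean that a partial loss of binding can remove a protein near the limit. Nor is PNGase F a defect in itself: the deamidation filter relies on that step.

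It may be said that the details sit in the cited method papers. Those are invoked for capture, digestion and instrument runs. How selective the lectin is for particular glycans cannot be judged here, but the comparisons themselves are fixed in section 2.13.

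Finally, site lists after PNGase F cannot recover glycan structure. That is correct, and it is why the analysis change needs the wording change with it.

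**Conclusion.** The point holds as a mismatch between the stated hypothesis and the planned readout. For a protein listed in all three pools, neither a change in glycan structure nor a difference in which sites are identified reaches the result of comparisons (4) and (5). Other glycosylation changes can reach it only by pushing a protein below the identification criteria in a pool, and a unique protein may have other causes, such as abundance.

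No percentage should be attached. To say that none of a change is visible on a protein seen in every pool would follow from the way the case is chosen, and a large enough loss of binding or occupancy would take the protein out of that case.

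The conclusion assumes that the comparisons are made as section 2.13 describes, on parent-protein lists. The section does not say that peptide or site data are destroyed, only that the lists compared are lists of proteins. The sponsor should act on this: the change is nearly free, and without it the planned results would not support a statement that pattern type alters glycosylation.

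**What to change.** 1. In section 2.13, run comparisons (3) to (5) also at the level of identified N-glycosites, that is, the deamidated peptides meeting the criteria in each pool. Keep the parent-protein list as a summary. Do not use the ratio of deamidated to unmodified signal as a measure of site occupancy: material is enriched on the lectin column before digestion, so unoccupied protein is largely depleted before it is measured.
2. In the Introduction, in section 2.7.2 and in the conclusions, restate the hypothesis and the claim as differences between pattern types in captured N-glycoproteins and N-glycosites. State that glycan structure is not assessed, and that a protein or site unique to one pool is a detection difference.

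Cost: analysis time and wording only, with no new samples or assays. The downside is longer lists and a narrower claim. The first change recovers site differences on shared proteins; it does not recover glycan structure, so the second is needed in any case.

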## Methods and analysis

2

### Study design and period

2.1

This observational trial will at first diagnose the pattern identification types of lung cancer patients with BCQ and then elucidate their relationships with proteomics. The study will be carried out in 2 groups; a lung cancer entire (LCE) group and a lung cancer representative (LCR) group, and these 2 groups will be described in further sections in detail. Figure 1 shows the schematic flow of this study.

**Figure 1 F1:**
[figure not shown]
Flow chart of the experimental methodology.

### Outcomes

2.2

#### Primary outcomes

2.2.1

1.Diagnosis of each pattern identification of Korean lung cancer patients with BCQs.2.Verification of the correlation of BCQ and blood on each patients’ pattern identification type through glycoproteomics.3.Protein identification and categorization by patients’ pattern identification for patient-specific diagnosis and medication in TKM.

#### Long term outcomes

2.2.2

(1)Diagnosis of the pattern identification of Korean patients with scientific basis.(2)Biomarker discovery on each pattern identification type of lung cancer patients within a large population.(3)Development and commercialization of precision medicine on each pattern identification type.(4)Tracking the efficacy of patient-specific treatments according to each pattern identification type with clinical proteomics in the follow-ups.

### Recruitment

2.3

Recruitment of participants began in September 2015, and the participants are lung cancer patients from Korea University Guro Hospital (Seoul, Korea). All patients are Korean males and females over the age of 18 years. Participants are recruited by a lung cancer doctor in the University Guro Hospital (Seoul, Korea) if they fulfill the eligibility criteria recommended by the investigators.

### Eligibility criteria

2.4

The inclusion and exclusion criteria of this trial are described in Table 1.

**Table 1 T1:**
[figure not shown]
The inclusion and exclusion criteria.

### Body constitution questionnaire (BCQ)

2.5

Pattern identification of a patient, expressed as either Yang or Yin, determines the patient's sensitivity for pathology. Yang deficiency (Yang-Xu) indicates a decrease of energy level in the physiological function of body and may cause fatigue, shortness of breath, chills, loose or watery stool, and polyuria.^[27]^ Yin deficiency (Yin-Xu) indicates a decrease in many physical aspects of human body including blood, interstitial fluid, and other bodily fluids and may result in thirsty, flush, dry stool, and decrease in urine output.^[26]^ Stasis is the inadequate transport of the physical aspects of the human body by energy due to the imbalance between Yin and Yang. Blood stasis and phlegm^[38]^ result from Stasis.^[28]^ Symptoms including joint pain, chest tightness or pain, lumps, and cough may arise. The BCQ(+), BCQ(−), and BCQ(s) questionnaires are developed in order to differentiate among Yang-Xu, Yin-Xu, and Stasis with a more objective method.^[26–28,39–41]^

